###### **3.2.2. Eligibility Criteria**

###### **3.2.3. Inclusion Criteria: Individuals eligible to be enrolled into this protocol are participants who:**

1. Meet Diagnostic and Statistical Manual-5th edition (DSM-5) criteria for current PTSD with a duration of 6 months or longer assessed by study psychiatrist;
2. Have a Clinician-Administered PTSD Scale for DSM-5 (CAPS-5) score of 50 or higher, indicating moderate to severe PTSD symptoms;
3. Between the ages 18 and 65, inclusive;
4. Are willing to refrain from taking any psychiatric medications during the study period, with the exception of gabapentin when prescribed for pain control. If the subject is on stimulants for attention-deficit/hyperactivity disorder (ADHD) at baseline, they can continue to use them at the same dose and frequency as long as they discontinue 5 half lives before the psilocybin session and do not restart for 10 days after psilocybin administration. Any psychoactive drugs, including stimulants, will be tapered in an appropriate fashion to avoid withdrawal effects. Medications will only be discontinued after consultation with the study psychiatrist;
5. Agree that, for one week preceding the psilocybin session, they will refrain from:
   1. taking any herbal supplement (except with prior approval of the research team);
   2. taking any nonprescription medications (with the exception of non-steroidal anti-inflammatory drugs or acetaminophen) unless given prior approval from the research team);
   3. taking any prescription medications (with the exception of birth control pills, thyroid hormones or other medications approved by the research team);
6. Refrain from the use of any psychoactive drug, with the exception of caffeine or nicotine, within 24 hours of the psilocybin session;
7. Agree not to use caffeine or nicotine for 2 hours before and 6 hours after the dose of psilocybin;
8. Agree not to use alcohol for 14 hours before and 24 hours after the dose of psilocybin;
9. Agree not to use benzodiazepines, hypnotics, and mood stabilizers for 12 hours before and 12 hours after the dose of psilocybin;
10. Agree not to use steroids for 2 weeks before and 2 weeks after the dose of psilocybin;
11. Agree not to use s-Adenosyl methionine (SAM-e), 5-Hydroxytryptophan (5-HTP), St. John’s Wort for 1 week before and 1 week after the dose of psilocybin;
12. Agree not to use cannabis for 1 week before and 1 week after the dose of psilocybin;

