###### **3.10.4. Safety Outcome Measures**

Safety measures will be applied as described below to minimize risks associated with study participation. The safety of participants will be assured before, during and after the psilocybin dosing session and during the study period by assessing physiological effects, psychological distress, concomitant medication use, medical events, spontaneously reported reactions, and suicidality. Therapists and study physician will be available via mobile phone throughout the study to ensure participant safety. Vital Signs (blood pressure, pulse, and temperature), Columbia Suicide Severity Rating Scale (C-SSRS), AEs and spontaneously reported reactions will be collected. All AEs, TEAEs, SAEs and AESIs will be collected from day 1 of treatment week until study termination. AEs may be collected during in-person visits or over the telephone or Zoom.

The **Columbia-Suicide Severity Rating Scale (C-SSRS)** is a clinician-administered measure of suicidal behavior devised to detect potential suicidal thoughts or behaviors during a clinical trial. It consists of a “Baseline” form that will assess suicidal ideation, ideation intensity, and behavior in the past 6 months, and a form for assessing current suicidal ideation and behavior. The C-SSRS consists of a series of questions and can be administered during a face-to-face interview or over the telephone. Suicidal ideation and behavior will be assessed at all visits. The C-SSRS Intensity scale for Lifetime obtained a Cronbach’s alpha of 0.93 and 0.94 for the Since Last Visit form, and Last Visit C-SSRS severity scores were positively correlated with the BDI “suicide thoughts” item [(91)](https://www.zotero.org/google-docs/?6SV43q).

**Figure 2.** Summarizes the study aims and presents the outcome measures for each aim.

[figure not shown]

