| **SCS-SF** |  |  |  |  |  | **╳** |  |  |  |  |  |  |  | **╳** |  |  |  | **╳** |  |  |  |  |  |  |  | **╳** |
| **CTQ-SF** |  |  |  |  |  | **╳** |  |  |  |  |  |  |  |  |  |  |  |  |  |  |  |  |  |  |  |  |
| **PIQ** |  |  |  |  |  |  |  |  |  | **╳** |  |  |  |  |  |  |  |  |  |  |  |  |  |  |  |  |
| **EBI** |  |  |  |  |  |  |  |  |  | **╳** |  |  |  |  |  |  |  |  |  |  |  |  |  |  |  |  |
| **ASC** |  |  |  |  |  |  |  |  |  | **╳** |  |  |  |  |  |  |  |  |  |  |  |  |  |  |  |  |
| **APEQ** |  |  |  |  |  |  |  |  |  | **╳** |  |  |  |  |  |  |  |  |  |  |  |  |  |  |  |  |
| **Oura Ring** |  | **╳** | **╳** | **╳** | **╳** | **╳** | **╳** | **╳** | **╳** | **╳** | **╳** | **╳** | **╳** | **╳** | **╳** | **╳** | **╳** | **╳** | **╳** | **╳** | **╳** | **╳** | **╳** | **╳** | **╳** | **╳** |
| **Qualitative survey** |  |  |  |  |  |  |  |  |  |  |  |  |  |  |  |  |  | **╳** |  |  |  |  |  |  |  | **╳** |
| **Safety and tolerability** | | | | | | | | | | | | | | | | | | | | | | | | | | |
| **Adverse events** |  |  |  |  |  |  | **╳** | **╳** | **╳** | **╳** | **╳** | **╳** | **╳** | **╳** | **╳** | **╳** | **╳** | **╳** | **╳** | **╳** | **╳** | **╳** | **╳** | **╳** | **╳** | **╳** |
| **Concomitant medications** | **╳** | **╳** | **╳** | **╳** | **╳** | **╳** | **╳** | **╳** | **╳** |  | **╳** | **╳** | **╳** | **╳** | **╳** | **╳** | **╳** | **╳** | **╳** | **╳** | **╳** | **╳** | **╳** | **╳** | **╳** | **╳** |
| **C-SSRS since last visit** |  | **╳** | **╳** | **╳** | **╳** | **╳** | **╳** | **╳** | **╳** | **╳** | **╳** | **╳** | **╳** | **╳** | **╳** | **╳** | **╳** | **╳** | **╳** | **╳** | **╳** | **╳** | **╳** | **╳** | **╳** | **╳** |

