###### **4.1. Adverse Events**

An AE is the development of an undesirable medical condition or the deterioration of a pre-existing medical condition following or during exposure to a pharmaceutical product, whether or not considered causally related to the product. An undesirable medical condition can be symptoms (e.g., nausea, chest pain), signs (e.g., tachycardia, enlarged liver) or the abnormal results of an investigation (e.g., laboratory findings, electrocardiogram). In clinical studies, an AE can include an undesirable medical condition occurring at any time, including run-in or washout periods, even if no study treatment has been administered.

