###### **4.1.6. Recording of Adverse Events**

AEs will be collected from day 1 of treatment week until the end of the study. At each visit, subjects will be asked if they have had any health problems since the previous visit. All AEs will be recorded appropriately, whether or not considered related to the investigational product. This will include AEs spontaneously reported by the patient and/or observed by the staff as well as AEs reported in response to a direct question e.g. “Have you had any health problems since your last visit?”

For each AE, the following parameters will be described: discovery (i.e., spontaneous or solicited); start; end date or ongoing; action taken with regards to investigational product; outcome if the AE caused the patient to discontinue; a statement if the AE fulfills the criteria for a SAE or not; the investigator’s assessment of the causal relationship between the event and the investigational product; intensity of the AE, i.e., mild (awareness of sign or symptom, but easily tolerated), moderate (discomfort sufficient to cause interference with normal activities), severe (incapacitating, with inability to perform normal activities); and resolution.

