###### **4.3. Prohibited Medications**

Psilocybin is contraindicated in participants who are on monoamine oxidase inhibitors or who have a known sensitivity to the drug or its metabolites. It is contraindicated in participants taking medications that are known as uridine diphosphate glucuronosyltransferase enzyme modulators. It is contraindicated in patients with schizophrenia or bipolar disorder, or in those with first degree relatives with these disorders. The concurrent use of selective serotonin reuptake inhibitors (SSRIs), serotonin-norepinephrine reuptake inhibitors (SNRIs) medications is assumed to be contraindicated due to the potential to increase the risk of serotonin syndrome and/or to attenuate the binding of psilocin to the HT2A receptor.

Participants must discontinue medications of medication classes listed in Table 4 at least 5 half-lives before baseline. Since the anticipated half-life of psilocybin is approximately 3 hours, no known issues related to pharmacokinetics or pharmacodynamic interactions are expected within approximately 7 days post-dosing. Common medications in these classes are noted in Table 4, but this list is not exhaustive. These medications must not be reintroduced to the participant until after end-of-study. The decision to discontinue these medications will be made by the participant and study psychiatrist.

**Table 4.** Prohibited Medications (Not an exhaustive list).

| Class | Common Medications |
| --- | --- |
| Selective-Serotonin Reuptake Inhibitors (SSRIs) | Citalopram  Escitalopram  Fluoxetine  Fluvoxamine  Paroxetine  Sertraline  Vilazadone  Vortioxetine |
| Selective-Norepinephrine Reuptake Inhibitors (SNRIs) | Desvenlafaxine  Duloxetine  Levomilnacipran  Milnacipran  Venlafaxine |
| Tricyclic Antidepressants (TCAs) | Amitriptyline  Amitriptylinoxide  Amoxapine  Clomipramine  Desipramine  Dibenzepin  Dimetacrine  Dosulepin  Doxepin  Imipramine  Lofepramine  Maprotiline  Melitracen  Nitroxazepine  Nortriptyline  Noxiptiline  Opipramol  Pipofezine  Protriptyline  Trimipramine |
| Other Antidepressants | Bupropion  Buspirone  Maprotiline  Mianserin  Mirtazapine  Nefazodone  Reboxetine  Setiptiline  Teniloxazine  Trazodone  Viloxazine |
| Monoamine Oxidase Inhibitors (MAOIs) | Bifemelane  Caroxazone  Isocarboxazid  Metralindole  Moclobemide  Moclobemide  Phenelzine  Pirlindole  Segeline  Toloxatone  Tranylcypromine  Rasagiline |

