###### **6.4. Informed Consent**

Participants will receive all information required by Health Canada/ICH guidelines, and must be informed that they may withdraw from the study at any time. Individuals must provide written, signed, and dated informed consent to participate in the study. Participants will not be coerced to complete study procedures. The study coordinator will provide them with information about the purpose of the study. The participants will be given sufficient time to read the informed consent form and ask any questions before deciding to participate. Participants who consent to participate in the study will then be asked to sign an informed consent form (ICF). Participants will sign the informed consent as the first step of the screening visit, before doing any study related activities. Additionally, at this visit, participants will be given the credentials of a dummy email account (an email address and password) created by the study team, which they will use to login to the Oura App (if applicable).

The specific consent process is as follows:

1. Informed consent must be obtained prior to any study-specific procedure being conducted on the patient.
2. Obtaining personal written informed consent:
   1. The information is to be given to the subject in written format, the ICF
3. Verify that the ICF given to the potential subject is the most recent REB-approved version of the consent for that clinical trial.
4. The ICF can be first presented to the patient by the study coordinator or other qualified personnel.
   1. The potential subject must be given ample time to read and understand the ICF.
   2. Study staff will then return and discuss the ICF with the potential patient, making sure to highlight important areas of the consent such as:
      1. The purpose of the study.
      2. Explain how many subjects will be involved.
      3. Discuss the duration of the study.
      4. Explain how many visits the subject will make.
      5. Discuss procedures; study intervention, device.
      6. Risks and possible benefits.
      7. Responsibilities of the investigator and subject.
      8. Any compensation to the subject.
      9. Notification of any other treatment available for the condition.
      10. That the subject has the right to withdraw.
      11. Confidentiality.

4. Promote the exchange of information with the subject and encourage any questions.

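### AE and SAE collection opens on Day 1, after the medication washout, so an event that starts and resolves between consent and Day 1 is not graded, assessed or tabulated as an AE

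*Protocol*

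**What the plan says.** Three places in the protocol set the start of AE collection, and they agree.

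- Section 3.10.4: "All AEs, TEAEs, SAEs and AESIs will be collected from day 1 of treatment week until study termination".
- Section 4.1.6, which governs recording: "AEs will be collected from day 1 of treatment week until the end of the study".
- Table 2 (section 3.12): the "Adverse events" row is blank from screening through baseline, and its first mark is at Day 1.

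Section 4.1 says that in clinical studies an AE can include an undesirable condition "occurring at any time, including run-in or washout periods, even if no study treatment has been administered".

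On medication, section 4.3 states: "Participants must discontinue medications of medication classes listed in Table 4 at least 5 half-lives before baseline". Section 3.13.5 places baseline one day before Day 1. Section 4.3 adds: "The decision to discontinue these medications will be made by the participant and study psychiatrist". Inclusion criterion 4 (section 3.2.3) says: "Any psychoactive drugs, including stimulants, will be tapered in an appropriate fashion to avoid withdrawal effects". Section 6.4 says: "Informed consent must be obtained prior to any study-specific procedure being conducted on the patient".

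Some information is gathered before Day 1. Table 2 schedules the C-SSRS and the concomitant medication review. Section 4 collects medical events, events leading to withdrawal and changes in psychiatric status over the whole study. Section 3.2.5 requires the reason for an early discontinuation to be documented in the CRF, and AE, serious or not, is one of the categories.

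**The concern.** Stopping psychiatric medication is a step that this design imposes on people with a CAPS-5 score of 50 or higher, and inclusion criterion 4 itself foresees withdrawal effects. That step lies in the part of the study where the protocol does not collect AEs.

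What is at stake is classification and tabulation. Tolerability, including the number and nature of AEs, is part of the primary objective (2.6.1), and the results are meant to inform a larger multi-site trial (7.1). A hospitalization during the washout could be known to the team and still be missing from the SAE table. Readers of the results would then see an incomplete account of what the treatment package, including its washout, asks of participants.

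**Working it through.** The plan gives no figure to reproduce. The check sets the sections side by side and counts marks in Table 2.

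**1. Order of events.** Consent precedes any study-specific procedure (6.4). The screening visit is about four weeks before the first therapy session (3.13.2). Table 4 drugs stop at least 5 half-lives before baseline (4.3). Baseline is the day before Day 1 (3.13.5), and AE collection opens on Day 1 (3.10.4, 4.1.6). A stop made for the trial under 4.3 therefore falls between consent and Day 1, outside the AE window.

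**2. Look-back at Day 1.** Section 4.1.6 asks about health problems since the previous visit. At Day 1 the previous visit is baseline, one day earlier, so the question does not reach an event that resolved earlier in the washout. An event still present on Day 1, or one that begins later, is captured.

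**3. Table 2.** Columns: screening 1, eligibility confirmation 1, pre-baseline weeks 3, baseline 1, treatment phase 8, weeks 2 to 13 12. Total = 1 + 1 + 3 + 1 + 8 + 12 = 26. Before Day 1: 1 + 1 + 3 + 1 = 6.

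| Row | Marks in all 26 columns | Marks in the 6 columns before Day 1 |
| --- | --- | --- |
| AEs | 8 + 12 = 20 | 0 |
| C-SSRS since last visit | 25 | 5 |
| Concomitant medications | 25 | 6 |

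The screening column, where the since-last-visit C-SSRS is blank, carries the lifetime and past-month form instead.

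**4. Length of the period.** About 4 weeks before Day 1 and 13 weeks from Day 1 to week 13: 4 / (4 + 13) = 4/17 = 23.5%. This is calendar time, not a share of events.

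**5. What each type of event receives under the current text.**

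- *Starts and resolves before Day 1, participant continues:* possibly known through the C-SSRS, the medication review or section 4. No 4.1.6 record (intensity, causality, seriousness, outcome) and no entry in the 7.1 tables.
- *Stops the participant before Day 1:* documented as a discontinuation reason, with AE available as the category (3.2.5). Neither the 4.1.6 fields nor tabulation is assured. The termination CRF page is required only for those who receive psilocybin.
- *Continues into Day 1 or starts later:* collected as an AE.

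**6. Causality scale.** The categories in 4.1.2 address only the relationship to psilocybin. Moving the start date alone would not get a washout event judged against the medication stop.

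**7. Primary criterion 5.** The limit is 20% of participants with AEs: 0.20 × 15 = 3 participants, and each participant is 1/15 = 6.7 percentage points. A longer AE window could move this rate, so its start should be fixed explicitly.

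**The case against.** The strongest reply is that Day 1 is a deliberate choice, stated three times without inconsistency, and that 4.1 is a general definition that sets no collection window. That is fair. A reader might infer that 4.1 flatly contradicts 3.10.4. It does not: 4.1 says what an AE can be, and 3.10.4 and 4.1.6 say when AEs are collected. The point is that the chosen window leaves out a period which 4.1 names and 4.3 makes mandatory.

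A second reply is that detection is already covered. This also stands. A reader might infer that washout events go unnoticed, but the C-SSRS, the medication review and section 4 argue against that. None of these, however, assigns the 4.1.6 fields or sends the event to the 7.1 tables.

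A third reply concerns participants who never reach Day 1. A reader might infer that the event stopping them leaves no trace as an AE. The protocol does not support that, because 3.2.5 documents the reason and has an AE category covering serious and non-serious events. Only the detailed record and the tabulation are not assured.

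Finally, few participants may be affected. Exclusion 15 removes people who need ongoing psychiatric drug therapy, and a pre-dose event cannot be a reaction to psilocybin, so expedited reporting under 4.1.11 is not in question. This limits the weight of the point but does not remove it.

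**Conclusion.** The point holds as a gap in how events are classified and reported. Following the plan as written, an AE or SAE that starts and resolves between consent and Day 1 gets no 4.1.6 record and stays out of the AE and SAE tables. One that stops a participant before Day 1 is documented as a discontinuation reason but is not assured either.

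The period has 6 of 26 schedule columns and about 4 of 17 weeks. The number of participants or events cannot be estimated: the protocol does not say how many will take a Table 4 drug at entry, when tapering starts, or how long 5 half-lives is for each drug.

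The conclusion assumes that the 7.1 tables are built from AEs collected under 3.10.4 and 4.1.6, and that a medication stop made for the trial follows consent. For stimulants, inclusion criterion 4 ties the stop to the dosing session, so theirs may fall later.

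No primary result is shown to be wrong. Correcting the gap is a cheap improvement to safety reporting and should be made.

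**What to change.** - In 3.10.4 and 4.1.6, collect AEs and SAEs from signature of the consent form to the end of the study. Section 3.9 already uses that start for concomitant medication.
- In Table 2, mark the AE row at the contacts before Day 1 that follow consent: screening (for events after consent), eligibility confirmation, pre-baseline weeks 1 to 3, and baseline.
- For these events, record the relationship to the required medication stop or to study procedures, since 4.1.2 covers only psilocybin.
- Tabulate pre-Day-1 events separately from events from Day 1 on and from TEAEs.
- State that primary criterion 5 keeps its Day 1 start, so the added period does not change the 3-of-15 limit.

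Cost: protocol wording and up to six marks in one row. The extra AE questions number 5 × 15 = 75 without the screening column, or 6 × 15 = 90 with it, plus one or two for each person who consents and proves ineligible (number not stated). All fall at time points that already carry the medication review, so no visit is added.

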###### **3.11. Quality Assurance**

Methods for quality assurance will be strictly observed. A start-up meeting involving all study site research coordinators, co-investigators, and partners will be held prior to the study launch. Further training will be held at each site prior to the commencement of the study. During training, great care will be taken to fully explain the study procedures and CRF completion.

###### **3.12. Participant Timeline**

**Table 2**. Schedule of Assessment.

| **Study Phases** | **Screening** | **Eligibility confirmation** | **Pre-baseline wearable monitoring (Oura)**** | | | **Baseline** | **Treatment Phase** | | | | | | | | **Follow-up** | | | | | | | | | | | |
| --- | --- | --- | --- | --- | --- | --- | --- | --- | --- | --- | --- | --- | --- | --- | --- | --- | --- | --- | --- | --- | --- | --- | --- | --- | --- | --- |
|  |  |  | **Week 1** | **Week 2** | **Week 3** |  | **Pre-Dose Period** | | **Dosing Day** | | **Post-Dose Period** | | | |  |  |  |  |  |  |  |  |  |  |  |  |
| **Assessment Days** |  |  |  |  |  |  | **Day 1** | **Day 2** | **Day 3**  **pre dose** | **Day 3 post dose** | **Day 4** | **Day 5** | **Day 6** | **Day 7** | **Week 2** | **Week 3** | **Week 4** | **Week 5** | **Week 6** | **Week 7** | **Week 8** | **Week 9** | **Week 10** | **Week 11** | **Week 12** | **Week 13** |
| **Screening** | | | | | | | | | | | | | | | | | | | | | | | | | | |
| **ICF signed** | **╳** |  |  |  |  |  |  |  |  |  |  |  |  |  |  |  |  |  |  |  |  |  |  |  |  |  |
| **Exclusion/inclusion criteria** | **╳** | **╳** |  |  |  |  |  |  |  |  |  |  |  |  |  |  |  |  |  |  |  |  |  |  |  |  |
| **Patient demographics and medical history** | **╳** |  |  |  |  |  |  |  |  |  |  |  |  |  |  |  |  |  |  |  |  |  |  |  |  |  |
| **Physical examination*** | **╳** |  |  |  |  |  |  |  |  |  |  |  |  |  |  |  |  |  |  |  |  |  |  |  |  |  |
| **Vital signs** | **╳** |  |  |  |  |  |  |  | **╳** | **╳** |  |  |  |  |  |  |  |  |  |  |  |  |  |  |  |  |
| **Contraceptive method review** | **╳** | **╳** |  |  |  | **╳** |  |  | **╳** |  |  |  |  |  |  |  |  |  |  |  |  |  |  |  |  |  |
| **Pregnancy screening** | **╳** |  |  |  |  |  |  |  | **╳** |  |  |  |  |  |  |  |  |  |  |  |  |  |  |  |  |  |
| **Urine & Blood Tests *** | **╳** |  |  |  |  |  |  |  |  |  |  |  |  |  |  |  |  |  |  |  |  |  |  |  |  |  |
| **C-SSRS lifetime and past month** | **╳** |  |  |  |  |  |  |  |  |  |  |  |  |  |  |  |  |  |  |  |  |  |  |  |  |  |
| **MINI** | **╳** |  |  |  |  |  |  |  |  |  |  |  |  |  |  |  |  |  |  |  |  |  |  |  |  |  |
| **Intervention** | | | | | | | | | | | | | | | | | | | | | | | | | | |
| **Psilocybin** |  |  |  |  |  |  |  |  | **╳** | **╳** |  |  |  |  |  |  |  |  |  |  |  |  |  |  |  |  |
| **Therapeutic Sessions** | | | | | | | | | | | | | | | | | | | | | | | | | | |
| **CPT (x2)** |  |  |  |  |  |  | **╳** | **╳** |  |  | **╳** | **╳** | **╳** | **╳** |  |  |  |  |  |  |  |  |  |  |  |  |
| **Preparatory Session** |  |  |  |  |  |  |  | **╳** |  |  |  |  |  |  |  |  |  |  |  |  |  |  |  |  |  |  |
| **Integration Session** |  |  |  |  |  |  |  |  |  |  | **╳** |  |  |  |  |  |  |  |  |  |  |  |  |  |  |  |
| **Efficacy** | | | | | | | | | | | | | | | | | | | | | | | | | | |
| **CAPS-5** | **╳** |  |  |  |  | **╳** |  |  |  |  |  |  |  | **╳** | **╳** |  |  | **╳** |  |  |  |  |  |  |  | **╳** |
| **PCL-5** | **╳** |  | **╳** | **╳** | **╳** | **╳** | **╳** | **╳** | **╳** |  | **╳** | **╳** | **╳** | **╳** | **╳** | **╳** | **╳** | **╳** | **╳** | **╳** | **╳** | **╳** | **╳** | **╳** | **╳** | **╳** |
| **PHQ-9** |  |  | **╳** | **╳** | **╳** | **╳** | **╳** | **╳** | **╳** |  | **╳** | **╳** | **╳** | **╳** | **╳** | **╳** | **╳** | **╳** | **╳** | **╳** | **╳** | **╳** | **╳** | **╳** | **╳** | **╳** |
| **GAD-7** |  |  | **╳** | **╳** | **╳** | **╳** | **╳** | **╳** | **╳** |  | **╳** | **╳** | **╳** | **╳** | **╳** | **╳** | **╳** | **╳** | **╳** | **╳** | **╳** | **╳** | **╳** | **╳** | **╳** | **╳** |
| **WHO-5** |  |  | **╳** | **╳** | **╳** | **╳** | **╳** | **╳** | **╳** |  | **╳** | **╳** | **╳** | **╳** | **╳** | **╳** | **╳** | **╳** | **╳** | **╳** | **╳** | **╳** | **╳** | **╳** | **╳** | **╳** |
| **WAI-SF** |  |  |  |  |  |  | **╳** | **╳** | **╳** | **╳** | **╳** | **╳** | **╳** | **╳** |  |  |  |  |  |  |  |  |  |  |  |  |
| **DES-II** |  |  |  |  |  | **╳** |  |  |  |  |  |  |  | **╳** |  |  |  | **╳** |  |  |  |  |  |  |  | **╳** |
| **PSQI** |  |  |  |  |  | **╳** |  |  |  |  |  |  |  | **╳** |  |  |  | **╳** |  |  |  |  |  |  |  | **╳** |
| **QRI** |  |  |  |  |  | **╳** |  |  |  |  |  |  |  | **╳** |  |  |  | **╳** |  |  |  |  |  |  |  | **╳** |
| **IPF** |  |  |  |  |  | **╳** |  |  |  |  |  |  |  | **╳** |  |  |  | **╳** |  |  |  |  |  |  |  | **╳** |
| **PMBS** |  |  |  |  |  | **╳** |  |  |  |  |  |  |  | **╳** |  |  |  | **╳** |  |  |  |  |  |  |  | **╳** |
| **BEAQ** |  |  |  |  |  | **╳** |  |  |  |  |  |  |  | **╳** |  |  |  | **╳** |  |  |  |  |  |  |  | **╳** |
| **MPFI-24** |  |  |  |  |  | **╳** |  |  |  |  |  |  |  | **╳** |  |  |  | **╳** |  |  |  |  |  |  |  | **╳** |
| **DERS-SF** |  |  |  |  |  | **╳** |  |  |  |  |  |  |  | **╳** |  |  |  | **╳** |  |  |  |  |  |  |  | **╳** |
| **SCS-SF** |  |  |  |  |  | **╳** |  |  |  |  |  |  |  | **╳** |  |  |  | **╳** |  |  |  |  |  |  |  | **╳** |
| **CTQ-SF** |  |  |  |  |  | **╳** |  |  |  |  |  |  |  |  |  |  |  |  |  |  |  |  |  |  |  |  |
| **PIQ** |  |  |  |  |  |  |  |  |  | **╳** |  |  |  |  |  |  |  |  |  |  |  |  |  |  |  |  |
| **EBI** |  |  |  |  |  |  |  |  |  | **╳** |  |  |  |  |  |  |  |  |  |  |  |  |  |  |  |  |
| **ASC** |  |  |  |  |  |  |  |  |  | **╳** |  |  |  |  |  |  |  |  |  |  |  |  |  |  |  |  |
| **APEQ** |  |  |  |  |  |  |  |  |  | **╳** |  |  |  |  |  |  |  |  |  |  |  |  |  |  |  |  |
| **Oura Ring** |  | **╳** | **╳** | **╳** | **╳** | **╳** | **╳** | **╳** | **╳** | **╳** | **╳** | **╳** | **╳** | **╳** | **╳** | **╳** | **╳** | **╳** | **╳** | **╳** | **╳** | **╳** | **╳** | **╳** | **╳** | **╳** |
| **Qualitative survey** |  |  |  |  |  |  |  |  |  |  |  |  |  |  |  |  |  | **╳** |  |  |  |  |  |  |  | **╳** |
| **Safety and tolerability** | | | | | | | | | | | | | | | | | | | | | | | | | | |
| **Adverse events** |  |  |  |  |  |  | **╳** | **╳** | **╳** | **╳** | **╳** | **╳** | **╳** | **╳** | **╳** | **╳** | **╳** | **╳** | **╳** | **╳** | **╳** | **╳** | **╳** | **╳** | **╳** | **╳** |
| **Concomitant medications** | **╳** | **╳** | **╳** | **╳** | **╳** | **╳** | **╳** | **╳** | **╳** |  | **╳** | **╳** | **╳** | **╳** | **╳** | **╳** | **╳** | **╳** | **╳** | **╳** | **╳** | **╳** | **╳** | **╳** | **╳** | **╳** |
| **C-SSRS since last visit** |  | **╳** | **╳** | **╳** | **╳** | **╳** | **╳** | **╳** | **╳** | **╳** | **╳** | **╳** | **╳** | **╳** | **╳** | **╳** | **╳** | **╳** | **╳** | **╳** | **╳** | **╳** | **╳** | **╳** | **╳** | **╳** |

**Abbreviations:** CAPS-5: Clinician-Administered PTSD Scale for DSM-5, PCL-5: PTSD Checklist-5, PHQ-9: Patient Health Questionnaire-9, DES-II: Dissociative Experiences Scale II, PSQI: Pittsburgh Sleep Quality Index, QRI: Quality of Relationships Inventory, IPF: Inventory of psychosocial functioning, PMBS: Posttraumatic Maladaptive Beliefs Scale, BEAQ: Brief Experiential Avoidance Questionnaire, MPFI-24: 24 items Multidimensional Psychological Flexibility Inventory, WAI-SF: Working Alliance Inventory- Short Form, DERS-SF: Difficulties in Emotion Regulation Scale-Short Form, SCS-SF: Self-compassion scale short form, PIQ: Psychological Insight Questionnaire, EBI: Emotional Breakthrough Inventory, ASC: Altered States of Consciousness Rating Scale, APEQ: Acceptance/Avoidance-Promoting Experiences Questionnaire, GAD-7: Generalized Anxiety Disorder Scale, 7-item, CTQ-SF: Childhood Trauma Questionnaire-short form, WHO-5: World Health Organization Well-Being Index, 5-item, CPT: Cognitive Processing Therapy, MINI: Mini International Neuropsychiatric Interview. * See section 3.13.2 for a thorough description. **Participants require to use a wearable (Oura) at least 3 weeks before baseline.

